### Data management

In order to meet regulatory requirements (Guidance for Computerized systems Used in Clinical Trials, International Conference on Harmonisation, Good clinical Practice 2001/20/CE), e-Case Report Formdesign, data monitoring and database extractions will be performed with Clinsight® software package.

### Statistical considerations

#### Estimation of sample size

Sample-size estimation is based on the comparison of early mortality rates at day 100 for two-sided α-risk and β equal to 5% and 20%, respectively, and a difference between the two randomised groups of 12%. Indeed, D100 mortality rate in allo-HSCT patients receiving PN with intravenous glutamine supplementation was set at 17% (considering data from the literature [1,23-25]) and the D100 mortality rate in EN patients with intravenous glutamine supplementation was set at 5%. Under these assumptions and considering D100 mortality at least equal to or lower than Seguy et al.'s studies (in which no patient received glutamine), 240 subjects are needed to show the superior efficacy of EN over PN in terms of D100 mortality. Two interim analyses are planned at n = 80 and and n = 160 patients (inflation of type I-error using Lan et Demets, Obrien-Fleming, East©). An independent committee will advise on continuation of the study according to results from these two interim analyses.

### Statistical analysis

The analyses will be conducted as intention-to-treat with Stata software (version 13, Stata Corp, College Station, US). All statistical tests will be considered for a type-1 error α of 5% (except the interim analyses). The continuous variables will be presented as their means and standard deviations according to statistical distribution (Shapiro–Wilk test), or as medians and interquartile ranges. The categorical parameters will be expressed as the number of subjects and associated percentages. The patients will be described and compared at inclusion according to the following variables: compliance with the eligibility criteria, epidemiological characteristics, clinical characteristics, biological characteristics and nutrition characteristics. Comparison between the two randomised groups concerning the primary endpoint will be analysed using the chi-squared test or exact Fisher's exact test, when appropriate. A logistic regression model will be performed to consider adjustments on baseline factors such as centre stratification parameters. Comparisons concerning other categorical criteria (*eg*. occurrence of GVHD or mucositis) will be realised as indicated previously. Comparisons between the two arms regarding quantitative criteria (*eg*. duration of nutrition intervention) will be assessed using Student's *t*-test (or the Kruskal–Wallis test, when appropriate). Initial number of days of hospitalization, number of transfers to the ICU and number of days of rehospitalization will be compared between groups, according to their statistical distribution using Poisson or negative binomial regressions. The censored data as survival rates (overall and progression-free, at one year) will be estimated by the Kaplan–Meier method and compared between randomisation groups using the log-rank test for univariate analysis and Cox's proportional-hazards regression for multivariate analyses. Finally, the follow-up of the clinical and biological parameters (nutritional: *i.e.* weight, body-mass index, brachial circumference, albumin and transthyretin; and inflammatory: C-reactive protein) collected at various times, will be analysed using mixed models 1) in order to take into account within and between patient variability (random-effects: slope and intercept) and 2) in order to study fixed effects : group, time and their interaction.

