**Table 2 Tab2:** **Schedule of visits and assessment**

	**Time point**										
	**D-14 to D-7**	**D1**	**D7**	**D14**	**D21**	**D28**	**D60**	**D90**	**D180**	**D270**	**D360**
**Informed consent**	**x**										
**Allocation**	**x**										
**Energetic and caloric needs assessment**			**x**	**x**	**x**	**-------------------------------------➔** ^**1**^					
**Digestive symptoms and tolerance** (individual notebook)		**x**	**--------------------------------------------------------- ➔** ^**2**^								
**Functional status** (Performance status, sit-up test, dynamometry, Weight, body-mass index, brachial circumference)	**x**			**x**		**x**	**x**	**x**	**x**		**x**
**Hepatic tolerance** (Total bilirubin, free and conjugated bilirubin, AST, ALT, ALP, GGT)	**x**		**x**	**x**	**x**	**x**	**x**	**x**	**x**	**x**	**x**
**Transthyretin, C-reactive protein**	**x**		**x**	**x**	**x**	**-------------------------------------➔** ^**3**^					
**Albumin**	**x**					**x**	**x**	**x**	**x**		**x**
**Clinical assessment** (GVHD, mucositis, infectious complications, red blood cells and platelets transfusions, catheter complications)			**x**	**x**	**x**	**x**	**x**	**x**	**x**	**x**	**x**
**Chimerism**						**x**	**x**	**x**	**x**		**x**
**Quality of life (QLQ-C30)**	**x**							**x**	**x**		**x**

^1^Evaluated until hospital discharge; ^2^Auto-evaluated daily during nutritional intervention; ^3^Evaluated once per week until hospital discharge; ALP: alkaline phosphatase; ALT: alanine aminotransferase; AST: aspartate aminotransferase; GGT: gamma-glutamyltransferase.

Such iterative and multiparametric evaluations are usually done and reported in all allo-HSCT trials. The three retrospective studies published in this specific "enteral nutrition / allo-HSCT" field(23–25) used the same methodology and criteria in order to correctly assess allo-HSCT complex and dynamic issues.

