Infectious complications will also be evaluated indirectly by assessing two events, which usually are almost exclusively related to infections within the allo-HSCT setting:The need for an ICU transfer, with severity evaluated using the following criteria: 1) clinically relevant and routinely used severity indexes (SOFA index, IGS2 score, D28 ventilator-free delay); 2) invasive ventilation and/or non-invasive need for ventilation; 3) extra-renal purification or need for dialysis; 4) length of stay in the ICU.The need to remove a central catheter.

Haematopoietic reconstitution will be specified using daily full blood-count results. Haematopoietic reconstitution will be valued by:Turnaround time of polynuclear neutrophils > 0.5 × 10^9^/L (first day within a period of 3 consecutive days).Spontaneous platelet turnaround time: >20 × 10^9^/L (2 days with no platelet transfusion within the previous 3 days).Spontaneous platelet turnaround time: >50 × 10^9^/L (2 days with no platelet transfusion within the previous 3 days).The number of transfusions of red blood cells and platelets between D0 and D100.

Engraftment rates will be evaluated by measuring chimerism (determined by molecular biology, i.e. analysis of variable non-tandem repeat segments, or sexual chimerism by FISH in the event of sex mismatches) at D30, D60, D90 and D180. This evaluation is usual in allo-HSCT follow ups

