### Nutritional outcomes

These criteria are usually not evaluated during the allo-HSCT procedure (except for weight and biological criteria), but will be specifically required for this prospective trial.

Nutritional status will be evaluated from clinical and biological criteria:Weight, body mass index and brachial circumference measured at D–7(*i.e*.7 days before treatment), once a week up to D28 or until hospital discharge, then once per month up to D180, and then at D270 and D360.Transthyretin and C-reactive protein (at D–7, then once a week during hospitalisation), albumin and C-reactive protein (at D–7, D7, D28, D60, D90, D180, D270 and D360).

Functional capacity (reflecting general condition and muscular efficiency, which can be easily linked to nutritional status) will be evaluated using the World Health Organisation Performance Status (0–4) and using the muscle strength measurement (on the upper limbs using a handgrip dynamometer, and on the lower limbs using the sit-up test) at D–7, D14, D28, D60, D90, D180 and D360.

The duration of the nutritional intervention, before resuming adequate oral feeding, will be defined by the number of days since the first day of EN or PN according to the randomisation group and the day of cessation of EN or PN (*i.e.* the patient had resumed oral feeding and was obtaining 75% of his/her protein-energetic needs). If patients in the EN group require PN supplementation, the duration of PN will be evaluated and compared with the PN group.

According to our previous unpublished experience, we do the assumption that morphometric measures and biological markers sould show a better nutritional status in EN group. In correlation with these results, functional status should be better in the EN group.

The randomized nutrition procedure is usually administered, on average, during 21 to 28 days: thus, we assume that improvement of nutritional status in EN group should be more relevant within the first 2 to 3 months after allo-HSCT, thereafter the difference between the two groups should be less important.

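### The secondary tests named for durations, GVHD and hospital days take no account of death, although the design assumes 17% versus 5% D100 mortality

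*Protocol article*

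**What the plan says.** The Statistical analysis section of the protocol article assigns methods by type of outcome.

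- **Occurrence outcomes**, with GVHD and mucositis as examples: chi-squared or Fisher's exact test, as for the primary endpoint.
- **Quantitative outcomes**: "Comparisons between the two arms regarding quantitative criteria", with nutrition duration as the example, use Student's t-test or Kruskal–Wallis.
- **Hospital use**: "Initial number of days of hospitalization, number of transfers to the ICU and number of days of rehospitalization will be compared between groups" by Poisson or negative binomial regression. No term for time at risk is mentioned.
- **Censored data**: Kaplan–Meier, log-rank and Cox, for overall and progression-free survival only.

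Nutritional outcomes gives the duration as "defined by the number of days since the first day of EN or PN" to the day support stops, and explains stopping as having regained oral intake at 75% of needs. Transplantation morbidity and mortality lists neutrophil and platelet recovery times and "The number of transfusions of red blood cells and platelets between D0 and D100", but names no test for them. Recovery times would fall under the general rule for quantitative outcomes.

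Estimation of sample size states that "D100 mortality rate in allo-HSCT patients receiving PN with intravenous glutamine supplementation was set at 17"% and that "D100 mortality rate in EN patients with intravenous glutamine supplementation was set at 5"%. The Discussion adds that D100 mortality has since fallen to about 10%, so the PN figure may be lower than planned.

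**The concern.** The trial is designed around a large difference in early death, yet the named secondary methods treat every patient as if observed to the end.

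A patient who dies on support never reaches the oral recovery that ends nutrition duration. A t-test must either leave that patient out or use the days up to death, which looks like early recovery. The same holds for neutrophil and platelet recovery if the general rule is applied. Days of the first stay end at death, and a patient who dies can accumulate no readmission days, so both are low for a bad reason. A death without prior GVHD counts as no GVHD.

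These outcomes are meant to explain any mortality effect. If EN does save lives, part of the difference on them would reflect longer survival and not more or less morbidity, and the stated tests cannot separate the two.

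**Working it through.** **Inputs from the article.** Total 240 with balanced groups, taken as 120 per arm; "two-sided α-risk and β equal to 5% and 20%, respectively"; D100 mortality 17% (PN) and 5% (EN); about 10% as a later figure; average support of 21–28 days. **Assumed**, because the article does not give them: timing of deaths, length of first stay, GVHD risk, ICU transfer frequency, and independence of death and morbidity unless stated.

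**The plan's own figure.** Two proportions, 0.17 versus 0.05, two-sided 5%, 80% power: the pooled formula gives 105.5, so 106 per arm (212 in all). With continuity correction it gives 121.6, so 122 per arm (244), within 2% of the stated 240. The mortality inputs are therefore those behind the design. Expected deaths: 120 × 0.17 = 20.4 and 120 × 0.05 = 6.

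**Days alive to D100.** If deaths are uniform over 100 days, mean days = 100(1 − q) + 50q = 100 − 50q.
- PN: 100 − 8.5 = 91.5. EN: 100 − 2.5 = 97.5. EN/PN = 1.066.
- At 10% versus 5%: 95.0 and 97.5, ratio 1.026.

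A constant death hazard gives 91.2 versus 97.5. With the same daily event rate in both arms, a count to D100 without an exposure term shows about 6–7% more events in EN.

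**Durations cut at death.** For a fixed duration L, the mean is L − q·L²/200.
- L = 25 (support): 24.47 versus 24.84, ratio 1.015.
- L = 40 (first stay, assumed): 38.64 versus 39.60, ratio 1.025.
- At 10% versus 5%: 1.006 and 1.010.

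Simulation with variable durations (means 24.5 and 40 days) and three patterns of death time gave PN/EN ratios of 0.98 for support and 0.96–0.97 for first stay.

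**GVHD by D100.** Assume a 40% risk in the absence of death and constant hazards: λg = −ln(0.6)/100 and λd = −ln(1 − q)/100. Observed proportion = λg/(λg + λd) × [1 − 0.6(1 − q)].
- PN 36.8%, EN 39.1%, EN/PN = 1.062.
- At 10% versus 5%: 38.1% and 39.1%, ratio 1.025.

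**Longer windows.** To D360 with no deaths after D100 (a strong assumption), days at risk are 307 versus 344, a PN/EN ratio of 0.89; at 10% versus 5% it is 0.95.

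**Direction for ICU transfers.** Assume survivors average 0.10 transfers and a share s of dying patients is transferred once: mean = 0.10(1 − q) + s·q.
- s = 0: PN 0.083, EN 0.095.
- s = 0.5: PN 0.168, EN 0.120.
- s = 0.8: PN 0.219, EN 0.135.

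The higher-mortality arm looks better in the first case and worse in the other two.

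**Does a D100 offset repair counts?** Suppose events occur only in D0–D28 at a constant rate. Mean days at risk in that window are 28 − q·28²/200: 27.33 and 27.80, ratio 1.017. An offset of days alive to D100 divides this by 1.066 and gives 0.955. A 1.7% distortion becomes one of 4.5% in the other direction.

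**The case against.** **Direction.** A reader might infer that the arm with more deaths will always look better on morbidity, so that the results are biased against EN. The article does not support this. Background names drug toxicity, infection and acute GVHD as the causes of early death, so many patients who die will already have had the event and be counted. The ICU calculation shows that the sign can reverse. This objection stands.

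**Size.** A reader might also infer serious inflation of the type I error. Any such figure needs event rates and dispersion that the article does not give, and constant rates to D100 are unfavourable for outcomes concentrated in the first month. For nutrition duration and first stay the shift is small. This also stands.

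**GVHD.** With complete follow-up to D100, cumulative incidence with death as a competing event equals the crude proportion that chi-squared already compares. The crude comparison is a legitimate description, and a Gray test would not remove the dependence on survival. A cause-specific model addresses it.

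**Left to an analysis plan.** Handling of deaths is often specified there, and no test is named for recovery times or transfusions. This stands in part: for recovery times the t-test is inferred from the general rule. But for nutrition duration, GVHD and hospital use the article does name the methods, and it reserves censored-data methods for survival.

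**Diaries.** Table 2 has symptoms "Auto-evaluated daily during nutritional intervention", and a reader might infer that the recording window differs by arm. Nothing in the article says so. The diary measures tolerance of the support itself, and weekly need for symptomatic treatment is assessed to discharge. It is a separate matter that would need new data collection.

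**Conclusion.** The point holds as a recommended change to the secondary analyses. Followed as written, the named methods drop deaths or score them as short or event-free, in a trial designed for about 20 versus 6 deaths per 120.

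Given equal underlying morbidity and death independent of it, the distortion at the planned mortality is about 2–3% for nutrition duration and first-stay days and about 6–7% for GVHD and for constant-rate counts to D100. It is roughly half of that or less at 10% versus 5%. It often favours the arm with more deaths, but the sign is not assured, least of all for ICU transfers. The comparison of D100 mortality is not affected.

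**What to change.** 1. Analyse end of nutritional support, neutrophil recovery and platelet recovery as time-to-event outcomes with death as a competing event, using cumulative incidence and the Gray test.
2. Keep the crude comparison of grade III–IV GVHD and add a cause-specific Cox model beside it.
3. Replace initial and repeat hospital days by days alive and out of hospital over a fixed window, for example to D100.
4. For other counts such as transfusions and ICU transfers, use an exposure offset only over the window in which the events occur, and only as a sensitivity analysis. Do not apply a D100 offset to every count. Show ICU transfers together with deaths.

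**Cost.** Slightly more analysis work and a change of wording. It relies mainly on dates of death, discharge, readmission, recovery and end of support, which the planned outcomes already require. Days alive and out of hospital mixes mortality with length of stay, so deaths, first-stay days and readmission days should also be shown separately by arm.

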## Discussion

The aim of this study is to evaluate the impact of nutritional support modalities during allo-HSCT on mortality and early immunological and infectious toxicities. Indeed, although the consequences of malnutrition are well known and nutritional support is recommended in the allo-HSCT setting, there is a lack of data on the best method of artificial nutrition, i.e. enteral or parenteral (ASPEN, European society of clinical nutrition and metabolism (ESPEN), SFNEP). The few data in the literature assume that EN may decrease early complications in allo-HSCT, notably infections and immunological issues, and decrease D100 mortality [23,24].

Rare data available in retrospective studies in this "enteral nutrition / allo-HSCT" field mentioned event rates for overall survival at D100 with myeloablative conditioning regimens respectively at 33% in PN group vs 8% in EN group, suggesting that 75% of early deaths could be avoided with EN. Even if these results can appear counter-intuitive considering solely correctable nutritional problems, it could be partially explained by recent scientific data suggesting that route of nutrition administration could impact on more than nutritional status. As instance, and even if these issues are not directly explored by our study, there are strong data suggesting an impact of nature and route of nutritional administration on dysbiosis [28-32], which has recently been shown to directly impact on post allo-HSCT survival [33].

The main evaluation criterion in this study is D100 mortality, which is a strong marker of early allo-HSCT toxicity, classically used in allo-HSCT trials; secondary criteria will evaluate haematological and nutritional outcomes. Therefore, we may be in the best position to evaluate the impact of EN on early allo-HSCT toxicity, and haematological and nutritional outcomes. Moreover, we have anticipated all the expected pitfalls related to allo-HSCT's intrinsic complexity and heterogeneity. In spite of these precautions, few limitations still remain: these are listed below.

EN in allo-HSCT needs the use of specific and adapted protocols, which have shown their efficacy and security in some centres [23-25]. The daily practical application of these precise and validated procedures requires experience. There is a risk that a lack of experience in some centres regarding NE administration after allo-HSCT may result in non-optimal use of EN, and lead to under-estimation of EN efficacy and tolerance. To avoid this risk, we have trained medical and paramedical teams in the main EN procedures, and have encouraged them to use EN before this trial began.

Furthermore, with the development and rapid spread of reduced-toxicity myeloablative conditioning regimens, early toxicity after allo-HSCT has decreased since this trial was first designed, reducing the D100 mortality to ~10% in the population with haematological malignancy [34]. Thus, toxicity in the PN group could be lower than expected according to our initial hypothesis: this may lead to an insufficient statistical power to demonstrate EN superiority.

## Trial status

The local ethical committee (CPP Sud Est VI) agreement was obtained in December 2012. The French national authorities (ANSM) agreement was obtained in July 2013. NEPHA recruitment has been ongoing since November 2013. Study completion date is estimated at June 2017. Clinical trials gov number: NCT01955772.

## Abbreviations

Allo-HSCT: Allogeneic hematopoietic stem cell transplantation
ANSM: French National Health Authorities
ASPEN: American society of enteral and parenteral nutrition
EN: Enteral nutrition
ESPEN: European society of clinical nutrition and metabolism
GVHD: Graft-versus-host disease
D100 mortality: Mortality at day 100
ICU: Intensive care unit
NEPHA: Comparison of Nutritional support with Enteral or Parenteral procedures in patients with Hematological malignancies undergoing Allogeneic stem cell transplantation
PN: Parenteral nutrition
SFNEP: French-speaking society of clinical nutrition and metabolism
